#### Statistical analysis

For our first two research aims, statistical analyses will be done on an intention-to-treat basis, with differences between study arms in mean changes in SBP and FRS as the primary outcomes. Participant characteristics and rates of recruitment, retention, and intervention fidelity will be summarized by using descriptive statistics. To test the hypothesis that the intervention will lead to significantly more reduction in SBP and FRS relative to the control condition, mean changes in SBP and FRS between baseline and 3-month and 6-month follow-up will be analyzed by independent t-tests between the 2 arms. Analysis of covariance and general linear modeling approaches will then be used to adjust for relevant covariates, such as gender, age, type of community, and baseline SBP and FRS values. Missing values for SBP and FRS at follow-up visits will be imputed by carrying forward baseline observations. If a covariate value is missing, it will be assumed to be missing at random. For sensitivity analyses, mean changes in SBP and FRS of participants who complete follow-up data collection will be analyzed by using a complete case analysis method. A stratified analysis will also be conducted within site or by gender to explore the potential impact of such factors on outcomes. In addition, data collected at all study visits will be modeled by repeated measures analysis of variance and linear mixed effects models, incorporating correlated data from multiple visits, to examine the post-intervention maintenance of SBP and FRS improvements. Determination of the appropriate covariance matrix in the repeated measure analysis will be based on quality of fit to the data by using the method of Fitzmaurice et al. [73]. Statistical analyses will be performed in SAS 9.4 (2015 SAS Institute Inc.). A two-tailed *p*-value <0.05 will be regarded as statistically significant.

To estimate whether the intervention effect is mediated by covariates, structural equation modeling will be performed by using Mplus [74], based on the following test for mediation: Intervention ➔ Mediator (path a), Mediator ➔ Outcome (path b). Intervention status (intervention vs. wait-list control) is a binary variable specified as exogenous (i.e., not predicted by other variables in the model). Covariates, including the Time 1 value of the mediator and potential confounders, can be specified along with intervention status, as appropriate. A postulated mediator is specified as predicted by the intervention effect (path a) and the BP outcome is predicted by paths from the mediator (path b) and a direct path from the intervention (path c). This yields coefficients for the 2 paths above and their standard errors, as well as an estimate of the direct effect (path c: intervention ➔ outcome).

The hypothesized mediation pattern is a significant path from the intervention to a given mediator (e.g., self-control), and a significant path from the mediator to a given outcome (e.g., SBP), indicating that at least part of the intervention effect is due to change in the mediator. The indirect effect is analyzed as the product of the two paths divided by an estimate of its standard error [75, 76]. Mediation can be tested for individual paths or a set of paths. Fritz and MacKinnon [77] have shown that the most powerful method to apply is the bias-corrected bootstrap test, available in Mplus. Simulations show that, with modest effect sizes (standardized coefficients of .20–.25) for path a and path b above, sample sizes in the range of 120–160 participants provide .80 power to detect an indirect effect that truly exists.

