### Definitively testing the effects of a hula-based intervention

With funding from the National Heart, Lung, and Blood Institute of the National Institutes of Health, we established the Kā-HOLO^1^ Project, a community-based participatory research (CBPR) project, to enhance the *Ola Hou i ka Hula* intervention (hereafter *Ola Hou*) by including an additional 3-month maintenance component. This component was informed by the self-regulation theory of behavior change [43], which emphasizes goal adoption for self-directed change, implementation of productive actions to achieve goals, and maintenance strategies to promote sustainable change by developing behavioral capability, self-control, and self-efficacy [44]. This approach has been successfully applied to HTN control in other populations [45, 46]. We then sought to perform a more definitive study of the effect of the intervention on HTN and CVD risk with a larger sample of Native Hawaiians. We developed a study protocol to address these 3 aims:

1) Test the efficacy of a 6-month hula intervention designed to reduce SBP in Native Hawaiians diagnosed with HTN by conducting an RCT with a wait-list control arm. *We predict that individuals in the intervention arm will have greater reductions in their SBP post-intervention compared with persons randomized to wait-list control, and will maintain these improvements at 12-month follow-up.*

2) Compare CVD risk scores in the intervention and wait-list control arms post-intervention and at 12-month follow-up. *We predict that NH randomized to the intervention will show greater improvements post-intervention in their 10-year CVD risk profile than those randomized to a wait-list control, and will maintain these improvements at 12-month follow-up.*

3) Test whether intervention effects are mediated through psychosocial and cultural factors by using structural equation modeling. *We predict that changes in these constructs will partially mediate the effect of the intervention on blood pressure reduction and CVD risk score, though a direct effect is also possible.*

The present article details the design and methodology of our ongoing intervention study. Subsequent publications will report the results.

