## Methods

### Study design

An overview of the study design appears in Fig. 1. We are conducting a 2-arm RCT using a wait-list control. We will recruit 250 adult Native Hawaiians with confirmed HTN and perform a 1:1 randomization within each study site, such that 125 are assigned to the intervention and 125 are assigned to the wait-list control arm. The hula intervention will be delivered by experienced *kumu hula* and trained community peer educators to groups of 12 to 15 at each study site following standardized protocols. Our primary outcomes are reductions in SBP and improvements in CVD risk as measured by the Framingham Risk Score (FRS). We elected to focus on SBP instead of DBP because the former is a stronger predictor of CVD risk, and its predictive strength increases with age [47–49]. Changes in SBP and FRS from baseline will be compared between study arms at 3-month and 6-month follow-ups. Wait-list participants will be offered the hula intervention after completing their 6-month follow-up. The original intervention arm will also complete a 12-month follow-up to assess the maintenance of SBP and FRS improvements.

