For all follow-up assessments, the same measures administered at baseline will be re-administered, with the exception of the sociodemographic measures, along with the mediator measures. At each visit, these measures will require 15 to 35 min to complete. For participants randomized to the intervention arm, follow-up data collection will happen at 3 months, 6 months, and 12 months. Collecting data at 3 months will allow us to compare the effects of the previously tested 3-month component against its effects in the ongoing RCT, while the 6-month follow-up will assess the effects of the add-on component intended to guide behavior change. The 12-month follow-up will assess post-intervention maintenance of SBP control. Participants in the wait-list control condition will contribute follow-up data only at 3 and 6 months. For control participants, the 3-month follow-up was designed to reduce attrition by keeping them engaged and providing an additional incentive to remain in the study. The efficacy of the hula intervention will be assessed by comparing baseline, 3-month, and 6-month data between intervention and control participants.

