#### Power analysis and sample size

Our proposed target of 250 enrolled participants (125 per arm) is based on an anticipated attrition rate of 20%. To test the efficacy of the intervention, our sample size calculation was based on mean differences in SBP in our pilot study [42], which demonstrated a 3-month mean change in SBP of 7.5 mmHg (SD = 16.5) between 2 arms randomized 1:1. Assuming that 206 participants (103 per arm) complete all follow-up assessments, we will have 90% statistical power to detect a similar effect size in our ongoing study.

Although we plan to compare CVD scores between the tow study arms, no FRS data specific to the Native Hawaiian population are available. Therefore, we used data from a previous community-based intervention to calculate the necessary sample size. In a 1-year study with a multiethnic sample recruited in medically underserved urban and rural communities (*n* = 195; 59% White, 37% Black, and 4% Hispanic), the biggest changes in FRS were observed at month four [59]. The reported average reduction in FRS varied according to differences in initial risk profiles – for example, 6.0% (SD = 9.9%) for participants at high risk (FRS ≥ 20) and 1.3% (SD = 4.5%) for participants at intermediate risk (20 > FRS ≥ 10). Among study participants, 63% had HTN, with baseline averages of SBP = 146 mmHg and DBP = 82 mmHg, almost identical to the baseline averages in our pilot study (SBP = 146 mmHg, DBP = 86 mmHg). Given a similar mean change in FRS for participants at intermediate risk, a sample of *n* = 206 will provide 80% statistical power to detect a change in FRS of 1.3% (SD = 4.5%) at 6-month follow-up.

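### Two primary outcomes are each tested at two visits at an unadjusted 0.05, and the plan does not fix which test decides efficacy

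*Protocol article*

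**What the plan says.** The Statistical analysis section covers the first two aims by intention to treat, "with differences between study arms in mean changes in SBP and FRS as the primary outcomes". Neither outcome is ranked above the other. To test the efficacy hypothesis, "mean changes in SBP and FRS between baseline and 3-month and 6-month follow-up will be analyzed by independent t-tests between the 2 arms"; covariate-adjusted models follow. The section's only decision rule is "A two-tailed *p*-value <0.05 will be regarded as statistically significant".

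On the time point, the document points both ways:

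- **Towards 6 months.** Aim 1 concerns a 6-month programme and predicts that "individuals in the intervention arm will have greater reductions in their SBP post-intervention compared with persons randomized to wait-list control". Aim 2 is worded likewise for CVD risk. The Power analysis section places the FRS calculation at the 6-month visit.
- **Towards both visits.** Study design states: "Changes in SBP and FRS from baseline will be compared between study arms at 3-month and 6-month follow-ups". Baseline and follow-up assessments ends with: "The efficacy of the hula intervention will be assessed by comparing baseline, 3-month, and 6-month data between intervention and control participants".
- **Towards 3 months.** The SBP sample size uses the pilot, "which demonstrated a 3-month mean change in SBP of 7.5 mmHg (SD = 16.5) between 2 arms randomized 1:1".

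**The concern.** Two outcomes at two visits make four between-arm tests of the primary outcomes, each at 0.05. The article does not say which of them carries the trial's main claim, or what happens if they disagree. A significant FRS difference at 3 months with nothing at 6 months, for example, could be reported as a positive primary result, and nothing in the text rules that out. The 5% error rate that the significance rule suggests would then not apply to the claim of efficacy.

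The choice also bears on the sample size. If a correction were added later by splitting alpha, the stated SBP power would no longer hold.

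**Working it through.** **1. The plan's own SBP power.** Inputs from Power analysis and sample size: difference 7.5 mmHg, SD 16.5, 103 per arm. Alpha is two-sided 0.05, from Statistical analysis.

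- Standard error = 16.5 × √(2/103) = 2.299; 7.5 / 2.299 = 3.262.
- Power = Φ(3.262 − 1.960) = Φ(1.302) = 90.4% (90.1% with the noncentral t).

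The stated 90% is reproduced, so it was computed with the full 0.05 on a single SBP test.

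**2. Family-wise error with independent tests.** Formula: 1 − 0.95^k.

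- k = 2 (both outcomes, 6 months): 1 − 0.95² = 9.75%.
- k = 4 (both outcomes, both visits): 1 − 0.95⁴ = 18.5%.

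**3. Family-wise error with correlated tests.** The tests are positively correlated. The same participants are measured twice, and SBP is entered into the FRS calculator. The documents give no correlation, so a range is assumed. One million draws of four normal test statistics were simulated with no true effect, each tested at |z| > 1.96. The correlation between different outcomes at different visits was set to the product of the visit and outcome correlations.

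| Assumed correlation | Two outcomes at 6 months (outcome correlation) | Four tests (visit and outcome correlations equal) |
|---|---|---|
| 0 | 9.8% | 18.6% (exact 18.5%) |
| 0.4 | 9.3% | 17.0% |
| 0.5 | 9.0% | 16.1% |
| 0.6 | 8.7% | 15.0% |
| 0.7 | 8.3% | 13.6% |
| 0.8 | 7.8% | 11.9% |
| 0.9 | 7.0% | 9.7% |

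Like the nominal 5%, these figures count false positives in either direction.

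**4. What splitting alpha would cost SBP** (103 per arm, same formula as step 1):

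- 0.025 per outcome at one visit: Φ(3.262 − 2.241) = 84.6%.
- 0.0125 for each of four tests: Φ(3.262 − 2.498) = 77.8% (77.0% with the noncentral t).

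A fixed sequence that starts with SBP at 0.05 leaves the 90.4% unchanged.

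**The case against.** The strongest reply is that 6 months is the natural reading. The aims speak of the end of a 6-month programme, and FRS is powered there. The assessment section also explains the 3-month visit as a comparison with the previously tested component and, for controls, as a way to limit attrition. This carries weight and makes two tests a fair reading. It does not close the matter. No passage labels 6 months as the deciding visit, the same assessment section ends by judging efficacy on both, and SBP is powered on a 3-month effect. Even with 6 months fixed, two outcomes at 0.05 give 7–10%.

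A second reply is that a p-value threshold is not a success criterion. The hypothesis joins SBP and FRS, and each has its own aim. If both had to succeed, or if each aim were a separate claim settled at 6 months, the inflation would not arise. That is correct. The article does not state an any-one-of-four rule; it leaves open which rule applies, so the error rates above are conditional on that reading.

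A third reply is that test order is commonly left to the SAP. That is fair, and it lowers the severity. But the article itself fixes the tests, the visits and one threshold for all, and its SBP power uses the whole 0.05.

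Some stronger readings are tempting but unsupported:

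- **A single inflated figure as a property of the trial.** A range such as 14–17% requires correlations of about 0.4–0.7, which the documents do not give.
- **Eight tests, counting the adjusted models.** The Statistical analysis section ties the hypothesis test to the t-tests and brings in adjustment afterwards.
- **SBP inside FRS as an aggravation.** Overlap raises the correlation and so reduces the inflation.
- **The pilot as evidence of a 3-month-only effect.** Its SBP drift came after a 3-month intervention had stopped, no between-arm contrast at 6 months is reported, and a genuine 3-month effect is not a type I error.

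**Conclusion.** The point holds. Two unranked primary outcomes, two visits and one unadjusted threshold leave the deciding test open. If any significant primary result counts as success, the family-wise error is about 7–10% on the narrower reading (6 months only) and about 10–18.5% on the wider one (both visits). Both ranges rest on assumed correlations of 0 to 0.9 and on no true effect on either outcome. Severity: should-fix, because the document leans towards 6 months, the inflation depends on how success is read, and wording alone settles it.

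**What to change.** Before any unblinded analysis, state in the protocol and SAP that:

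1. the first primary test is the between-arm difference in SBP change at 6 months, at two-sided 0.05;
2. FRS change at 6 months is tested at two-sided 0.05 only if the SBP test is significant;
3. the 3-month SBP and FRS comparisons are secondary;
4. one model, either the t-test or the covariate-adjusted analysis, is the basis of each claim, and the other is a sensitivity analysis.

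This holds the family-wise error for the two primary claims at 5% whatever the correlation. It needs no added participants or data, and SBP keeps its full alpha and stated 90% power. The cost is that FRS cannot be claimed if SBP fails. If the investigators prefer equal standing for the two outcomes, a split of 0.025 each at 6 months also controls the error, but it lowers SBP power to 84.6%. A both-must-succeed rule needs no split, but the trial's power is then limited by the weaker of the two tests.

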### Pilot study and preliminary findings

We conducted a pilot randomized controlled trial (RCT) with a wait-list control group to test the effects of a 3-month hula-based intervention on reducing SBP in 55 Native Hawaiians and other Pacific Islanders with physician-diagnosed HTN and SBP >140 mmHg (or >130 mmHg for those with comorbid diabetes) [42]. The intervention was called *Ola Hou i ka Hula* (Restoring Health Through Hula), and it involved 2 60-min hula lessons per week delivered over 12 weeks, along with 6 30-min sessions on HTN self-management delivered between the hula lessons. Each hula group consisted of 12–15 participants. At 3-month follow-up, 72% of intervention paticipants demonstrated ≥10 mmHg reduction in SBP, versus 39% in the wait-list control group. The mean SBP reduction was −18.3 mmHg for the intervention group versus −7.6 mmHg for controls. The intervention group also reported significantly more reductions in bodily pain and improvements in social functioning, along with a reduction in perceived ethnic discrimination [42]. However, at 6-month follow-up (3 months after cesssation of the intervention), SBP in the original intervention group began to return to baseline.

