#### Retention and incentive plan

All participants will receive a gift card incentive equivalent to $25 at each data collection visit, with total incentives of $100 for completing all 4 visits. For the wait-list control arm, the fourth payment will be an incentive to start the *Ola Hou* program at month 12. This strategy will ensure that all participants receive the same dollar amount of incentives, thereby avoiding any perception of unfairness – an important consideration in close-knit Native Hawaiian communities. Intervention participants will also receive an ambulatory upper-arm band BP device (valued at $40) to monitor their progress, which they can keep after the study is completed. Wait-list control participants will receive the same device when they begin the intervention. Reminder calls or emails will be made to both intervention and control participants 1 week before each data collection visit, and follow-up calls or emails will be made to allow participants who miss a data collection visit to reschedule. Participants who miss a visit and do not reschedule will be considered dropouts, and study staff will attempt to re-engage them. In our pilot study, these retention strategies successfully retained 87% of participants over a 3-month period. They should be similarly effective over the 12-month period required by the ongoing study [42].

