#### Protections against risk

One of the protection procedures for the participants is to obtain written approval by their personal physician before enrolling in the study to ensure they can participate in moderate physical activity safely. Having this approval will ensure they are also seen by their physician and that the physician is aware of participation in this study, providing the opportunity for a medical evaluation of his/her HTN (important for those who have not seen their physician within the past 6-months). A protocol will be established in the event that a participant’s blood pressure exceeds a safe level, systolic blood pressure > 180 mmHg or diastolic blood pressure > 110 mmHg, either during an assessment or during self-monitoring while in hula lesson. If BP exceeds the above cut off points, participants will wait 5 min and will be measured again. If BP is still elevated, they will be asked to go home and see their doctor as soon as possible. The participant will then be allowed to re-enter the study when cleared by their primary physician and no longer symptomatic; provided that this is done within 2 weeks. All adverse events will be immediately reported to the Principal Investigator and the DSMB for review and follow-up.

Trainings will be held for kumu hula and community peer educators, conducted by a clinician, to teach the symptoms and signs of physical distress, such as headache or blurred vision, confusion, chest pain, shortness of breath, dehydration, and edema. They will be taught how to handle these issues and when medical or emergency services are required. In the rare case that the intervention or data collection causes psychological distress, the Principle Investigator, who is a licensed clinical psychologist, will be consulted. He will meet with the participant to debrief and to determine if a referral to another mental health professional is necessary for further follow-up.

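### Carrying the baseline value forward for every missing SBP and FRS is a poor primary rule: it shrinks the effect, and it biases the comparison either way if dropout differs by arm

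*Protocol article*

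**What the plan says.** The Statistical analysis section of the protocol article says of the first two aims that "statistical analyses will be done on an intention-to-treat basis, with differences between study arms in mean changes in SBP and FRS as the primary outcomes". Mean changes from baseline to 3 and 6 months "will be analyzed by independent t-tests between the 2 arms", followed by covariate-adjusted models. The significance rule is "A two-tailed *p*-value <0.05 will be regarded as statistically significant".

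The missing-data rule is explicit and covers both primary outcomes: "Missing values for SBP and FRS at follow-up visits will be imputed by carrying forward baseline observations". A complete-case analysis is named as the sensitivity analysis. Linear mixed models using all visits appear in the same section, but their stated purpose is to look at maintenance after the intervention.

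Three other places bear on the point:
- **Pilot study and preliminary findings:** "The mean SBP reduction was −18.3 mmHg for the intervention group versus −7.6 mmHg for controls".
- **Inclusion and exclusion criteria:** entry requires SBP above 140 mmHg, or above 130 with diabetes.
- **Power analysis and sample size:** 90% power is claimed for 206 completers (103 per arm) out of 250 enrolled, for a difference of 7.5 mmHg with SD 16.5 and 20% anticipated attrition.

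**The concern.** Carrying baseline forward sets the change to exactly zero for anyone without a follow-up value. That is a strong statement about what happened to them, and the plan's own evidence speaks against it. Pilot controls, who had not had the programme, still fell 7.6 mmHg. A sample selected on raised SBP is expected to fall somewhat whatever the arm. Someone seen at 3 months but not at 6 is also scored at baseline for the 6-month comparison, although a later measurement exists.

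The estimated difference then mixes the treatment effect with the pattern of missing visits. With equal dropout it is pulled towards zero. With unequal dropout, the arm that loses more people looks worse than it is, so the rule cannot be defended as simply conservative. In addition, the power statement concerns completers at the full effect, while the analysis described as primary covers all 250 with imputed zeros.

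**Working it through.** **Inputs from the protocol article.** 125 per arm randomised; 206 completers; difference 7.5 mmHg; SD 16.5; two-sided alpha 0.05; pilot control change −7.6. Dropout is 20% as stated, or 1 − 206/250 = 17.6% as implied by the completer count.

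**Assumptions.** Dropouts would have changed like completers. Mean changes are −15.1 (intervention) and −7.6 (control); −15.1 is the pilot control change plus the planned 7.5, and is not itself a figure in the article. Unequal dropout splits are illustrative.

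**Step 1: the plan's own figure.** SE = 16.5 × √(2/103) = 2.30; 7.5/2.30 = 3.26; power = Φ(3.26 − 1.96) = 90.4%. The stated 90% reproduces for completers. With 100 per arm (20% dropout, no imputation) it is 89.5%.

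**Step 2: the analysis as planned.** For an arm with true mean change μ and dropout d:
- mean after imputation = (1 − d)μ
- variance after imputation = (1 − d)SD² + d(1 − d)μ²

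Equal 20% dropout:
- Difference: 0.8 × 7.5 = 6.0 mmHg.
- Variances: 0.8 × 272.25 + 0.16 × 15.1² = 254.3, and 0.8 × 272.25 + 0.16 × 7.6² = 227.0.
- SE = √((254.3 + 227.0)/125) = 1.96; 6.0/1.96 = 3.06; power = Φ(1.10) = 86.4%.

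Equal 17.6% dropout gives 0.824 × 7.5 = 6.18 mmHg and 87.7% by the same steps.

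The power depends on the assumed arm means:

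| Mean changes (intervention, control) | Power, 20% dropout | Power, 17.6% dropout |
|---|---|---|
| −7.5, 0 | 88.9% | 89.8% |
| −15.1, −7.6 | 86.4% | 87.7% |
| −18.3, −10.8 | 84.5% | 86.2% |

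The loss is modest because the imputed zeros also reduce the SD (to 14.9–15.9 at 20% dropout) and the analysed number rises to 125 per arm.

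**Step 3: no true effect, both arms falling 7.6 mmHg.**

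| Missing, intervention / control | Spurious difference favouring hula | Type I error |
|---|---|---|
| 20% / 20% | 0 | 5.0% |
| 15% / 25% | 7.6 × (0.85 − 0.75) = 0.76 mmHg | 6.8% |
| 10% / 30% | 7.6 × (0.90 − 0.70) = 1.52 mmHg | 12.6% |

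For the last row, SE = √((250.2 + 202.7)/125) = 1.90, z = 0.80, and the two tail areas are 12.3% and 0.3%.

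**Step 4: true effect 7.5 mmHg, more loss in the intervention arm.**
- 25% / 15%: 15.1 × 0.75 − 7.6 × 0.85 = 4.9 mmHg; power 69%.
- 30% / 10%: 15.1 × 0.70 − 7.6 × 0.90 = 3.7 mmHg; power 47%.

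Simulated t-tests (40,000 trials per scenario) agreed where run: 86.1% and 87.6% power for 20% and 17.6% equal dropout; type I error 4.9%, 6.7% and 12.9% for the three rows of Step 3.

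**FRS.** The same multiplier applies: the planned 1.3 points becomes 0.8 × 1.3 = 1.04 at equal 20% dropout.

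**The case against.** Much can be said for the plan. The 90% is correct for the completers it describes, and with equal dropout the planned analysis loses only a few points. If the effect is the 10.7 mmHg gap between the pilot arm means (18.3 − 7.6), power at 20% dropout is about 99% even with the imputation. Return to baseline also has some support for people who leave the intervention, since pilot SBP began to drift back once the programme ended. Complete-case analysis is planned, and the mixed models would use the observed 3-month values. All of this stands. It limits the size of the problem, but it does not justify zero change for controls or make the rule a good primary choice.

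Three stronger readings are tempting, and the documents do not support them:
- **That missingness will be unbalanced because controls have little reason to return.** No dropout by arm is given. Controls receive the programme only after the 6-month visit, both arms have payments, reminders and rescheduling, and the control 3-month visit was designed to limit attrition. Where the Retention and incentive plan says "Participants who miss a visit and do not reschedule will be considered dropouts", it adds that staff will try to re-engage them.
- **That the blood-pressure safety rule removes intervention participants selectively.** The cut-offs apply "either during an assessment or during self-monitoring while in hula lesson", so assessments in both arms count. Re-entry is allowed "provided that this is done within 2 weeks", but nothing says that outcome visits end for those not cleared, and no frequency is given. The point is speculative and forms no part of this finding.
- **That the power claim collapses.** At equal dropout it does not.

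**Conclusion.** The point holds in this form: baseline-carried-forward is a weak primary rule for both primary outcomes, and a better analysis is already in the plan.

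The firm part is the shrinkage. At the plan's own attrition, 7.5 mmHg is estimated as 6.0–6.2, and power for the planned analysis is some 0–6 points below the stated 90%. This rests on dropouts changing like completers.

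The more serious part is conditional. If dropout differs by arm, the error can favour either arm, and a spurious effect of about 1 mmHg with an inflated type I error becomes possible. How far depends on splits that the documents do not give. The article states the rule outright, so this is not a matter of detail left to an analysis plan.

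**What to change.** Make the linear mixed model already named in the Statistical analysis section the primary analysis for the 6-month arm contrast. Its terms would be baseline value, site, visit and arm-by-visit, fitted to all observed 3- and 6-month values of SBP and, separately, FRS. State that the carry-forward rule does not feed this model. Keep baseline-carried-forward and complete-case as sensitivity analyses, ideally with one missing-not-at-random analysis, such as a delta adjustment.

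Restate power for the analysis chosen. Without imputation, the completer figures (90.4% with 103 per arm, 89.5% with 100) are the natural starting point. Keeping baseline-carried-forward as primary would need about 130–149 per arm for 90% at 20% dropout.

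The cost is a wording change before unblinded analysis; no new data are needed, and the model is already planned. The downside is reliance on missing-at-random, which may credit intervention dropouts with continued benefit although pilot SBP drifted back after the programme ended. The retained baseline-carried-forward analysis shows how much that matters.
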